
## Section G: Sample Size/Data Analysis

### G1. Sample Size

How many subjects (or specimens, or charts) will be used in this study?

Local: 455      Worldwide: 455

Please indicate why you chose the sample size proposed:

The proposed sample size of 455 includes 425 patients and 30 clinicians.

The sample size of clinicians was determined by creating a schedule for the expected flow of Veteran participants in the study that predicts expected demand for coaching.

In determining the sample size of patients for the study, we examined the number of patients needed to have adequate power for both hypotheses related to the primary aim (specific aim 1). The sample size determined for the primary aim was inflated to account for potential correlation of patients treated by the same PCP and to account for attrition at 1 year of 25%, based on our and other prior VA studies.

The sample size is based on testing for a clinically important difference between the two groups at a single time point, using a two-group t test with a 0.05 two-sided significance level and power of 80%. For HbA1C, a difference of 0.5 is considered clinically significant within a 6-month time frame. Using a difference score of 0.5 in the mean HbA1c between the two groups and an estimated pooled standard deviation of 1.1 results in

an effect size,  $d = .45$ . This effect size is consistent with our prior RCT study on behavioral coaching interventions which generated HbA1c level differences of 0.68 and a medium effect size of 0.50 and estimates from our HOPE pilot confirm these effects. Using these data, a sample size of 79 per group or 158 total would be needed for a significant difference in the proportion of participants achieving greater than or equal to 0.5 improvement in HbA1c.

For PHQ-9, a score of less than 10 or a 5-point decline from baseline would be considered a clinically significant improvement. The sample size of 79 per group would have 80% power to detect a change as small as 1.5 points in the PHQ-9 score with a two-sided  $\alpha = 0.05$ . From our own work using cognitive-behavioral therapy for medically ill Veterans with depression, we found clinically significant improvements in Beck Depression Scale scores consistent with effect sizes of 0.98 at 8 weeks and 1.05 at 20 weeks post-intervention. This level of efficacy is consistent with our estimates of clinically significant change as indicated by PHQ-9 scores.

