Following the approach of Schnurr et al, we inflated the sample size to account for a correlation among patients seen by the same PCP using the formula,  $f = 1 + (m - 1)\bar{r}$ , where  $m$  is the average number of patients per provider and  $\bar{r}$  is the intra-class correlation coefficient. Assuming there will be 40 to 50 PCPs results in  $m = 4$  and estimating  $\bar{r}$  as .05 yields  $f = 1.15$ . This inflation factor is modest but reasonable, given the nature of the study and the extent of the external clinical providers' involvement (supported by personal communication with [name] – May 2010).

Thus, the sample size needed for analysis is 182 total (91 per group). Finally, adjusting this for 25% attrition using the inflation factor of 1.33 [i.e.,  $1/(1-.25)$ ] gives a total of 242 patients to be recruited. Therefore, a final cohort of 182 at 12-month follow-up (i.e., recruitment of 242 to allow for 25% attrition) would provide sufficient power to conduct analyses for Aim 1. This sample would provide 80% power to detect an effect size of 0.45, which represents a difference in HbA1c of 0.5 with a standard deviation of 1.1 and a difference in PHQ-9 scores of as little as 1.5 with standard deviation of 3.4.

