Independent Evaluators (IE) who are blinded to the study procedures and treatment assignments will collect data at 6 and 12 months by phone. They will mail assessment packets to participants and then work with them to complete all self-report items. IEs will arrange a lab visit for a blood draw within 2 weeks before and 2 weeks after the target data-collection time (facilitated by PCPs). If PCPs have already obtained A1c levels in that timeframe, those values will be used. Participants will receive modest compensation after A1c results and self-report assessments are collected. RAs will also perform chart abstraction of clinical baseline, moderating, and exploratory variables. Data Quality Assurance: Using previously developed and standardized procedure manuals, providing rigorous training and fidelity measurement of study coaches and independent evaluators, as well as providing written guides for assessments are ways quality will be assured. Attrition/Retention and Missing Data: We expect rates of missing data for primary outcomes less than 25%, leading to primary outcome data for greater than 75% of participants. To evaluate the potential relationship between loss to f/u and outcome variables, reasons for study discontinuation will be recorded for subsequent analyses, and overall attrition rates will be factored in the analyses of the primary specific aim. We will conduct sensitivity analyses using tests for data missing completely at random and tests for nonrandom missingness. We will also plot the data over time to visually assess changes in outcomes from baseline to 12 mos. and to indicate whether additional terms are needed in the models to account for nonlinearity over time. Data Analysis Plan: Primary Analyses: A1c and Depression Outcomes--We will compare participants in the two study arms on baseline characteristics, including sociodemographic characteristics (age, race/ethnicity, gender, education level, independent living status, VA copay status, employment status) and clinical variables (BMI, Deyo comorbidity score, psychotropic and diabetes medications and treatments, specific psychiatric diagnoses, and number of PCP visits in the previous 12 mos). Based on recommendations of the CONSORT group, we will not provide tests of significance or adjust subsequent analyses for variables found to differ because adjustment may bias the estimated treatment effect. However, the analyses for the primary aim will be adjusted for variables we have decided a priori may be important to control: a) baseline values of HbA1c and PHQ-9, b) whether the patient was on exogenous insulin, and c) the stratification variable, site. In addition, we will compare participants on d) access to psychotherapy and medication, defined as dichotomous variables. At baseline, 6 months, and 12 months, we will construct variables for whether the patient was receiving

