
psychotherapy during the previous 6 months (yes/no), whether psychotropic medications were started or changed during the past 6 months (yes/no), and whether insulin was added during the past 6 months (yes/no). A1c and Depression Outcomes at 6 months--The patients' A1c levels and PHQ-9 scores at 6 months will be the primary outcomes. We will examine the normality of the distributions of these outcomes and will consider transformations such as the log or the inverse, if necessary. Separate models will be run for HbA1c and for PHQ-9. We will run hierarchical linear model analyses to account for the correlation of patients being seen by the same PCP. Using this nested approach, we will test if there are differences between EUC and the HOPE intervention, using the A1c level and the PHQ-9 score (either untransformed or transformed, if needed) as dependent measures. Although patients are also nested within coach, the coaches are not assigned exclusively to certain PCPs. We will include intervention fidelity scores for each coach as a study variable in our analysis of this aim to account for coaching fidelity effects. Each model will contain a variable indicating the treatment group, indicator variables representing site, whether or not the patient was on exogenous insulin (evidence suggests that insulin use impacts both A1c and depressive symptoms), receiving psychotherapy, taking psychotropic meds, and baseline A1c or PHQ-9 levels as independent variables. A significant value for the treatment group variable in the hierarchical model will indicate that there were statistically significant differences between the intervention and EUC. In addition, we will examine whether the groups differed as to whether or not they had clinically significant changes in A1c and PHQ-9 by dichotomizing the outcomes. A significant decrease for A1c is defined as 0.5 between each time point and from baseline to 12-months. For PHQ-9, this will be a change score of 5 or greater at 6- and 12-months. We will test whether the two groups (clinically significant change vs. no change) differed using a hierarchical logistic-regression model in which the dichotomous outcomes are the dependent variable. The independent variables will be those described above for the hierarchical linear regression. A1c and Depression Outcomes at 12-months-- The patients' A1c levels and PHQ-9 scores at 12-months will be the primary outcomes. Similar to the analyses at 6 months, we will examine the distribution and run hierarchical linear models on the 12 month data. In addition, we will examine all of the time periods in a hierarchical longitudinal analysis, separately for A1c and PHQ-9. This random coefficient model will allow us to fit a line for each participant using his/her available data, including participants with missing values, and will maximize the power to detect differences because patients are not removed from the analysis if any of the time periods is missing. Patients will be nested with their PCP. The model will contain the A1c and PHQ-9 values for each of the time periods (baseline, 6 and 12 months). The independent variables in the model will be time, treatment, the interaction of time and treatment, site, and use of exogenous insulin psychotropic meds, or psychotherapy. The treatment effect will measure differences between the intervention and EUC groups at baseline, and the time effect will measure whether there was an overall change over time in the two clinical outcomes. The time-by-treatment interaction is of most interest in the longitudinal analysis because a significant value will indicate that there was a difference between the intervention and EUC groups over the 12-month time period. Mediators and Moderators: To examine the role of potential moderators and mediators on intervention effectiveness, we will evaluate factors that mediate and moderate outcomes at 6 and 12 months. Moderating variables are those that specify on whom and under which conditions treatments have different effects. The moderating variables for this aim include sociodemographic traits, BMI, medical and psychiatric comorbidity, and social support. Mediator variables identify possible mechanisms through which a treatment achieves its effect. Mediators include the GET-D scores for goals and action plans, diabetes-related distress, self-efficacy, performance of self-care behaviors, and adherence to pharmacological therapy. We will consider the difference between the moderators and mediators in terms of when they occur relative to treatment and whether they are correlated with treatment. Moderators must precede treatment and should not be correlated with treatment. Mediators will occur during treatment and should be correlated with treatment. Thus, we will initially test for the association of the moderating and mediating variables with treatment. Since the treatment is a dichotomous variable, we will use t tests to determine if continuous moderators or mediators are associated with treatment and chi-square tests to determine if ordinal or categorical moderators or mediators are related to treatment. After verifying that a possible moderator is not significantly related to treatment, we will run the model, including a term in the model for the moderator and a term for the interaction of that variable with treatment. A significant value for the interaction term will indicate that the effect of treatment on the individual patients depends on their value of the moderator. For mediators, we will test if the variable has either a main or interactive effect on the outcome. With an emphasis on the effect size of treatments and what influences the effect size for a particular moderator or mediator, we will calculate effect sizes at each of the scheduled time points. In addition, we will form response categories to assess the stability of variables under two approaches to measuring outcomes (one using continuous variables for outcomes and the second using categories for the outcomes). For example, we might define an improvement in A1c as a decrease of 0.5 from baseline or PHQ-9 decrease of 5 from baseline. We would then run the analytic models using the dichotomous variable of whether or not the patients' A1c level improved as the outcome variable. If the two-variable presentations prove to be similar, we will likely use the categorical approach because of greater ease in reporting results to

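### The supporting longitudinal Aim 1 model leaves the arms' baseline means free and has no baseline covariate, so its treatment-by-time test is not baseline-adjusted and loses about 10 power points if the baseline correlation is 0.5

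*Protocol*

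**What the plan says.** G2 (Primary Analyses) sets a general rule: "the analyses for the primary aim will be adjusted for variables we have decided a priori may be important to control: a) baseline values". The values meant are those for the two outcomes, HbA1c and PHQ-9; insulin use and site are listed as well. The 6-month hierarchical linear models follow it, with baseline A1c or PHQ-9 as a covariate. The 12-month single-timepoint models are to be run in the same way.

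For the 12-month outcomes G2 then adds a random coefficient model, fitted separately to HbA1c and PHQ-9, whose responses are the values at baseline, 6 and 12 months. On its terms G2 says "The independent variables in the model will be time, treatment, the interaction of time and treatment, site". Insulin, psychotropic medication and psychotherapy use complete the list. No baseline value of the outcome is among the covariates. The treatment term is explained thus: "The treatment effect will measure differences between the intervention and EUC groups at baseline". The interaction of time and treatment is named as the term of greatest interest.

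**The concern.** If the treatment main effect is the arm difference at baseline and is left free, each arm has its own baseline mean. The interaction then compares change from baseline between arms, without regression adjustment for baseline. Under F2 Procedure, patients are randomised only after the baseline assessment and blood draw, so the expected baseline difference is zero. Estimating it adds variance and removes no bias.

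Two things are at stake. First, this model does not follow G2's own adjustment rule, whereas the single-timepoint models do. Second, it is the Aim 1 model that G2 describes as keeping patients with a missing visit, and the plan allows for 25% attrition. It is the natural model to turn to when data are incomplete. Yet it gives a less precise answer than the same data allow, and it can differ from the adjusted 12-month model because of chance imbalance at baseline.

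**Working it through.** **Inputs from the protocol (G1).** The basis is a single-timepoint comparison "using a two-group t test with a 0.05 two-sided significance level and power of 80" percent. The HbA1c target is given as "a difference in HbA1c of 0.5 with a standard deviation of 1.1". For the depression outcome the corresponding target is "a difference in PHQ-9 scores of as little as 1.5 with standard deviation of 3.4". Before inflation, "a sample size of 79 per group or 158 total would be needed". The design effect is 1.15, with 91 per group analysed, 242 recruited and 25% attrition. F1 plans 60:40 allocation.

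**Assumed, because the protocol does not give it.** The correlation rho between baseline and follow-up, varied from 0.3 to 0.8. The SD is taken as equal at every visit.

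**Step 1: reproduce the plan's figure.** A two-sample t test with d = 0.45 and 79 per group has power 80.3%; with 78 per group it has 79.7%. So 79 is right. Then 158 × 1.15 = 181.7, giving 182, and 182 × 1.33 = 242.06, giving 242. The effective number per arm after clustering is 91 / 1.15 = 79.1, so 79 is used below.

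**Step 2: variance of each contrast.** With complete data, per patient:
- free baseline (change from baseline): 2·SD²·(1 − rho)
- baseline-adjusted, or common baseline mean with categorical visits: SD²·(1 − rho²)
- ratio, adjusted to free: (1 + rho)/2, which is 0.75 at rho 0.5, a 25% reduction.

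**Step 3: standard errors for HbA1c.** The SE of a plain difference in means is 1.1 × √(2/79) = 0.175. At rho 0.5 the free-baseline SE is 0.175 × √(2 × 0.5) = 0.175, and the adjusted SE is 0.175 × √0.75 = 0.152.

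**Step 4: power (noncentral t, 79 per arm, two-sided 0.05).**

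| rho | HbA1c, as written | HbA1c, adjusted | PHQ-9, as written | PHQ-9, adjusted |
|---|---|---|---|---|
| 0.3 | 67% | 85% | 64% | 82% |
| 0.4 | 74% | 87% | 71% | 85% |
| 0.5 | 81% | 91% | 79% | 89% |
| 0.6 | 89% | 94% | 87% | 93% |
| 0.7 | 96% | 98% | 94% | 97% |
| 0.8 | 99% | 100% | 99% | 100% |

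With 182 patients split 60:40 and the design effect applied, HbA1c power at rho 0.5 is 79.5% as written and 89.5% adjusted.

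**Step 5: incomplete data.** With all 242 patients, 25% missing at 12 months and rho 0.5, generalised least squares gives a loss of 7.4 to 8.7 points. The range covers linear or categorical time and two correlation structures.

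**Step 6: effect of a chance imbalance.** Relative to the adjusted estimate, the free-baseline estimate shifts by (1 − rho) times the baseline imbalance. For an imbalance of one standard error (0.175) at rho 0.5, that is 0.5 × 0.175 = 0.088, or 0.088 / 0.5 = 17.5% of the target difference.

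**Step 7: does it matter how the main effect is removed?** These are generalised least squares results with three visits, compound symmetry, rho 0.5 and 79 per arm. Each entry is the expected estimate of the 12-month effect.

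| True effect at 0, 6, 12 months | Free baseline, linear time | Common baseline, linear time | Common baseline, categorical visits |
|---|---|---|---|
| 0, 0.25, 0.5 | 0.500 | 0.500 | 0.500 |
| 0, 0.5, 0.5 | 0.500 | 0.545 | 0.500 |
| 0, 0.5, 0.25 | 0.250 | 0.318 | 0.250 |

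The standard errors are 0.175, 0.149 and 0.152 respectively. A common baseline with linear time is biased at 12 months when the effect plateaus or fades; categorical visits are not.

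**The case against.** The best case for the plan is that nothing confirmatory is affected. G2 names HbA1c and PHQ-9 at 6 and at 12 months as the primary outcomes and tests them in models that carry the baseline value. The sample size rests on a single-timepoint comparison. The longitudinal model is introduced as an addition, and a free baseline mean per arm is a valid and common parameterisation. All of this stands and limits the weight of the point. It does not explain why a model placed under the primary analyses departs from the adjustment rule stated there.

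The size of the loss also depends on an assumption. At rho 0.5 the model as written has 81% power, about the planned 80%; it falls below a plain comparison of 12-month means only when rho is under 0.5. By rho 0.7 the loss is about 2 points, and by 0.8 it is negligible. That stands too.

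A reader might infer several stronger things that the documents do not support:
- **That the interaction test is biased, or that a baseline imbalance passes wholly into the treatment effect.** Under randomisation the contrast is unbiased, and the shift relative to the adjusted estimate is (1 − rho) times the imbalance.
- **That G2's claim of maximum power for this model is false.** The reason given there is that patients with a missing visit are retained. It is not a claim to be better than baseline adjustment.
- **That the treatment term breaks the promise that "we will not provide tests of significance or adjust subsequent analyses for variables found to differ".** That sentence follows a list of sociodemographic and clinical characteristics which does not include HbA1c or PHQ-9. G2 says only that the treatment term measures a baseline difference and announces no test of it.

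**Conclusion.** The point holds as a matter of efficiency and consistency in one supporting model. As written, the treatment-by-time test is an unadjusted change-from-baseline contrast, out of line with G2's rule on baseline adjustment. For HbA1c the cost is about 17 to 18 power points at rho 0.3, 10 at 0.5, 6 at 0.6 and 2 at 0.7. If all 242 patients contribute and 25% are missing at 12 months, the loss at rho 0.5 is about 7 to 9 points.

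These figures rest on an assumed rho and on equal SDs across visits. The entry thresholds on HbA1c and PHQ-9 may narrow the baseline spread and lower the correlation. It would be too strong to say that Aim 1 as a whole lacks baseline adjustment, because the single-timepoint models at both visits have it. The change is worth making because it costs almost nothing.

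**What to change.** Respecify the longitudinal model in one of two ways:

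1. Treat time as categorical visits, give both arms a common baseline mean (no treatment main effect), and estimate separate treatment effects at 6 and 12 months.
2. Use only the 6- and 12-month values as responses, with baseline A1c or PHQ-9 as a covariate and treatment-by-visit effects.

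Keep site in either version. Do not simply delete the treatment main effect while time stays linear. F1 plans six months of coaching followed by six without, so a plateau or fade is plausible, and that shortcut would then misstate the 12-month effect. Do not add baseline as a covariate while it remains a response, because that uses it twice. Delete the sentence that reads the treatment term as a baseline difference.

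The cost is a short rewrite of the model specification, including the move from fitted lines to visit effects. No new data, patients or visits are needed.

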training workshop, after feedback with study staff (~6mos post-workshop), at exit from the study. Coaches also complete 2 surveys about experience with each veteran (Sect. S, WAI-C and CEC-C) to be administered ~4 mos. after assignment. Survey responses will be entered into a fillable form on a password protected M: drive folder accessible to study staff and coaches (a separate folder from that which contains ID-name link). No PHI or sensitive data will be entered. Once complete, surveys will be entered by staff into a database on the M drive for analysis. Identifying Patient Participants: The study sample will be identified and enrolled using a multi-step screening process. An initial pool of eligible patients with diabetes will first be identified by VISN 16 Data Warehouse and randomly assigned as potential participant lists stratified by clinical site. Information/PHI to be used in this initial data pull that may identify a subject include name, address, phone #, year of diabetes dx and the dates/values of most recent A1c. This info will be used to determine poor glycemic control as an inclusion criterion and to contact the subject to complete the next steps in the screening process. Birth date, race, ethnicity, and gender will also be collected in the initial data pull as descriptive statistics to determine if there are statistically significant differences between interested and not interested patients. The location of the patient's PC facility and their doctor's name will be collected in the initial data pull to identify subjects to guide randomization and coach pairing after randomization respectively. A waiver of informed consent/HIPAA authorization has been approved by the IRB on 2/15/2012 for this initial step of the screening process (Sect S). We will take all measures necessary to ensure the confidentiality/anonymity of all participants. Patients who meet criteria for uncontrolled diabetes and geographic location will receive an opt-out letter about the study. Patients who do not opt out will be contacted by study personnel for the second step of the multi-step screening process. Study RAs will then use a structured, phone-based screening interview to identify patients who preliminarily meet our depression inclusion criteria on the abbreviated PHQ-8 scale. The screening interview will also exclude from that group who screens positive on the PHQ-8 but for whom a phone-based intervention would be inappropriate. Specific procedures and measures to be administered can be found in HOPEIIR Screening Procedures (Sect S). After completing the detailed screening, patients who still meet eligibility will be approached for informed consent and a baseline assessment. The PHQ-9, as part of the baseline assessment, will serve as the final eligibility check in this multi-step screening procedure. Following the phone screening, interested and preliminarily eligible patients will be mailed a copy of the ICF w/out signature lines, along with the baseline measures. After the patient has time to review these docs, study staff will call the patient on the phone to go over the informed consent process. The patient will have the opportunity to ask questions and must demonstrate an understanding of the risks and benefits of participation before verbal consent to participate is achieved. After consent, the subject will begin the baseline assessment. Because this intervention will be used in the medical care of participants, subject's participation in this protocol will result in their medical records being flagged. The following Title 38 U.S.C. 7332 protected information will be collected for scientific research purposes as part of this research protocol: drug and/or alcohol abuse. This info will be maintained in accordance with the security requirements of 38 CFR Section 1.466, or more stringent requirements. This info will not be re-disclosed except back to the VA. This info will not identify any individual patient or research subject in any report of the research, or otherwise disclose patient or research subject identities. The purpose of collecting alcohol and or drug abuse and treatment info (38USC7332) is to conduct scientific research. No personnel involved, in this study, will identify, directly or indirectly, any individual patient or subject in any report of such research or otherwise disclose patient or subject identities in any manner. Baseline Assessment: Subjects who meet eligibility criteria during the phone screening procedures and give verbal consent will participate in a baseline assessment. All assessments (baseline/ 6- /12-month f/u) will be completed by a blinded independent evaluator (IE) over the phone. Baselines will begin with a socio-demographic survey, followed by the PHQ-9 and a myriad of other measures (see HOPEIIR Baseline and Follow Up Measures document in Sect S). A1c collection will be coordinated by IEs. Lab collection is feasible, with high completion rates in our prior VA studies. In EPIC, A1c collection was higher than survey collection rates. All participants who do not meet the final A1c eligibility criteria but were identified as having significant depressive symptoms will be notified of their results, and a note will be placed in their medical record indicating this finding to their PCP. Enrolled participants will also have a note placed in their medical record indicating the presence of clinically significant depressive symptoms and the results of their most recent A1c labs. The participant will be provided with materials on diabetes and depression, and the participant and PCP will be given evidence-based recs for treatment of the depressive symptoms. After baseline, participants will receive \$30. Measures will be repeated from the baseline assessment at 6 and 12-mos., but no demographics. If staff cannot reach a veteran 3x by phone to schedule f/up, a letter may be sent. Packets will be mailed to participants as a courtesy for each assessment so that they may follow along with the measures as they are administered by phone (Sect S). Randomization: All consented participants who complete the baseline and are eligible after baseline and blood draw will be randomized to HOPE or Enhanced Usual Care. Eligible participants at each site will be randomly assigned by a RA following the baseline evaluation. In accordance with VA policy and procedures, participants randomized to the HOPE intervention will receive VHA Form 10-3203 (Sect S) with

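### Mediator tests for the exploratory Aim 2a leave out the mediator's own baseline value, which costs power and can let stable patient traits pass as mechanisms

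*Protocol*

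**What the plan says.** Section G2 (Mediators and Moderators) names as mediators the GET-D goal and action-plan scores, diabetes distress, self-efficacy, self-care behaviours and medication adherence. It says that mediators arise during treatment and ought to be related to it, and tests that relation first: "we will use t tests to determine if continuous moderators or mediators are associated with treatment". Ordinal and categorical variables get chi-square tests. The second step reads: "For mediators, we will test if the variable has either a main or interactive effect on the outcome".

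No baseline mediator value is mentioned in either step. The baseline scores that G2 lists for its outcome models are those of A1c or PHQ-9. For those two outcomes the same section uses hierarchical models with the baseline score, site and the PCP level.

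On data collection, section F2 says: "Measures will be repeated from the baseline assessment at 6 and 12-mos., but no demographics". The instrument list itself is in an attachment that is not shown. Section D labels Aim 2 as exploratory.

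**The concern.** The effect of HOPE on a mediator is a randomised comparison of a repeated score, just as for A1c and PHQ-9. Yet the mediator test drops the baseline score, site and PCP, all of which the primary models use. Where a score is stable over time, ignoring its baseline leaves explainable variance in the error term, and real effects of HOPE on a mechanism are more easily missed. A chi-square test on an ordinal mediator also discards the ordering.

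The outcome step carries a different risk. The mediator is not randomised. A patient with high distress before treatment may have high distress and a high PHQ-9 afterwards. If baseline distress predicts later outcome over and above the baseline outcome, the follow-up mediator picks up that trait and can look like a mechanism.

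At stake is what Aim 2a reports about how HOPE works. The Aim 1 comparison of the arms is not touched.

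**Working it through.** **The protocol's own sample size (section G1).** Inputs: two-sided 0.05, 80% power, two-group t test, d = 0.45.
- The exact t test gives 78.5 per group, so 79 ("a sample size of 79 per group or 158 total would be needed").
- Clustering by PCP: 1 + (4 − 1) × 0.05 = 1.15, and 158 × 1.15 = 181.7, so 182 analysed.
- Attrition: 182 × 1.33 = 242.1 ("gives a total of 242 patients to be recruited").

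These figures reproduce. No power is stated for the mediator analysis. Section F1 allocates 60:40, so 182 completers split as 109.2 : 72.8, taken as 109:73.

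**Step 1: power of the treatment-mediator test.** Assumed, not in the protocol: a true effect of 0.35 SD and a baseline/follow-up correlation r of 0.5 to 0.7. With √(109 × 73 / 182) = 6.612, the noncentrality is 6.612 × effective d, on about 180 degrees of freedom. Effective d is
- 0.35 for the t test on follow-up scores,
- 0.35/√(2(1 − r)) for the t test on change scores,
- 0.35/√(1 − r²) with baseline adjustment.

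| r | t test, follow-up | t test, change | baseline-adjusted |
|---|---|---|---|
| 0.5 | d 0.350, 63% | d 0.350, 63% | d 0.404, 76% |
| 0.6 | d 0.350, 63% | d 0.391, 73% | d 0.438, 82% |
| 0.7 | d 0.350, 63% | d 0.452, 84% | d 0.490, 90% |

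At a 91:91 split, the follow-up t test gives 65% against 77-91% adjusted. If the protocol's factor of 1.15 is applied at 0.4 SD, the figures are 69% against 81-93%.

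**Step 2: false acceptance, by simulation.** The mediator has no effect on the outcome, there are 109:73 patients, and the outcome model contains arm and baseline outcome. Two assumed structures were tried.

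*Direct prediction.* The baseline mediator predicts the later outcome by g SD given the baseline outcome; baseline mediator and baseline outcome correlate 0.3; 4,000 trials per setting; PCP clustering not simulated. Each cell gives the rate without / with the baseline mediator.

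| HOPE effect on mediator | r | g | outcome step | both steps |
|---|---|---|---|---|
| 0.4 SD | 0.5 | 0 | 5% / 5% | 4% / 5% |
| 0.4 SD | 0.5 | 0.15 | 20% / 5% | 15% / 4% |
| 0.4 SD | 0.5 | 0.30 | 58% / 5% | 42% / 4% |
| 0.4 SD | 0.7 | 0.15 | 36% / 5% | 27% / 5% |
| 0.4 SD | 0.7 | 0.30 | 88% / 5% | 65% / 5% |
| none | 0.7 | 0.30 | 89% / 5% | 4% / 0.2% |

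*Shared trait.* Latent traits drive mediator and outcome at both times, with a cross-sectional correlation of 0.3-0.4, r of 0.5-0.7 and an outcome correlation over time of 0.5; 1,500 runs per setting. The outcome step alone is falsely significant in 67-95% of trials without the baseline mediator and in 19-62% with it. Both steps together, as planned: 3-5% if HOPE does not move the mediator, about 43-57% if it moves it by 0.35 SD. With baseline adjustment the latter falls to about 15-35% in most settings, and to 46% at the highest in the most strongly correlated ones.

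**Effect on true mediators.** With a 0.4 SD effect of HOPE on the mediator and a 0.3 SD effect of the mediator on the outcome, the chance of passing both steps rises from about 75% to 85% (r = 0.5) or 90% (r = 0.7). The outcome step alone loses a little power, from nearly 100% to 94-99%.

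**The case against.** Three stronger readings are tempting, and the protocol does not support them.

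First, a reader might infer that the t test is applied to the raw follow-up score. G2 does not say whether it is that or the change from baseline. With change scores the power gap narrows to 6 points at r = 0.7 (84% against 90%) and stays at 13 points at r = 0.5.

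Second, a reader might infer that a mediator failing the first test is dropped. G2 states such a rule only for moderators; for mediators it is at most implied. If nothing is dropped, the test is still the planned evidence that HOPE moved the mediator, so the loss of power matters either way.

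Third, a reader might take 67-95% as the rate of false mediators. That is the outcome step alone. Where HOPE does not move the mediator, requiring both steps holds the joint rate at 5% or less. Where the baseline mediator adds no prediction of the outcome, there is no inflation at all.

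It also stands that the correlations and trait structures are assumptions, that baseline availability is inferred because the instrument list is not shown, and that the document identifies no specific ordinal mediator. Omitting site and PCP costs mainly efficiency. G2 nowhere excludes baseline mediators, and a separate analysis plan could add them. But the unadjusted tests are named in the protocol, so this is a stated choice of method as well as detail left open.

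**Conclusion.** The concern holds as a weakness of method in an exploratory aim. Under randomisation the t test keeps its 5% level, so the first harm is lost precision: at 0.35 SD, 13 to 27 points of power against an adjusted analysis if follow-up scores are tested, and 6 to 13 points if change scores are. The second harm is conditional. It needs a mediator that HOPE moves, that does not affect the outcome, and whose baseline or underlying trait predicts the outcome beyond baseline A1c or PHQ-9. This is plausible for distress, self-efficacy and self-care, but it is not shown in the document.

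The direction is the same in both simulated structures, while the size depends on which one is true. Baseline adjustment restores the error rate under direct prediction and only reduces it under a shared trait. The change is worth making before the mediator analysis is run.

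**What to change.** For Aim 2a, and only for mediators measured in both arms with a baseline value (not GET-D scores if they have none):

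1. Replace the t and chi-square tests of mediators by a model of the Aim 1 form: follow-up mediator on arm, baseline mediator and site, with the PCP effect. Use an ordinal model for any ordinal mediator.
2. In the outcome model, include the baseline mediator beside the follow-up mediator and the baseline outcome.
3. State that this reduces but does not fully remove confounding of the mediator-outcome relation, and report mediator findings with that caution.

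The cost is a few sentences in G2. If the baseline measures are collected as F2 indicates, no new data and no extra patients are needed.
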